#### Imaging substudy

Because the imaging analysis is a novel investigation, its analysis will be iterative and relatively open-ended; the choice of statistical analyses is likely often to depend on the results obtained in preceding analyses. Statistical analysis of the imaging data will be performed in three parts, all using 24-week data: (1) Development of an objective scoring technique based on receiver operating characteristic curve methodology, (2) Assessment of the relationship between continuous severity scoring of the disease and imaging parameters and (3) Comparison of imaging parameters between the aganirsen exposure arms and placebo. Two thirds of the data of all arms combined will be used to develop the objective scoring methodology. This will comprise the ‘learning’ dataset. One third of the data will not be included in the initial analysis and will be retained as the ‘validation’ dataset. Objective imaging parameters (e.g. area of iris covered by neovessels) will be related to NVG diagnosis using a stepwise logistic regression. The final model will retain imaging parameters with *P* ≤ 0.10, including interactions. Each subject will receive a score generated by the final model.

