*BCVA* best-corrected visual acuity, *EDTRS* Early Treatment Diabetic Retinopathy Study, *EQ-5D* EuroQoL five dimensions questionnaire, *IEC*, *Independent Ethics Committee*, *IOP* intraocular pressure, *NEI*-*VFQ-25* National Eye Institute Visual Function questionnaire 25, *RAPD relative afferent pupillary defect*, *SD-OCT* spectral domain optical coherence tomography

^a^Pregnancy tests may also be repeated as per request of IECs or if required by local regulations. Only applicable for women of childbearing potential

^b^Optional at all other visits: only if neovascularisation is suspected in slit lamp examination, gonioscopy or indirect ophthalmoscopy

^c^IOP measurement by Goldmann applanation tonometry can be performed at any time of the day at the screening visit, V9 and at an unscheduled visit. The time (±1 h) of IOP measurement at the baseline visit is mandatory for all other visits (V3–V8)

^d^Perimetry can be skipped if eligibility is fulfilled by other criteria

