Additional exclusion criteria were defined for the eligibility of patients for the risk factor substudy: age 65 years or older, renal insufficiency and acute malignant or inflammatory reaction (systemic or local).

The co-primary efficacy endpoints combine a neovascularisation component: presence of anterior segment neovascularisation (NVI or NVA), NVD and/or NVE in the study eye requiring PRP rescue treatment or cryotherapy rescue treatment up to week 24 scored dichotomously (yes/no) and an IOP component: percentage change (≥20%) in IOP compared to baseline and >21 mmHg in the study eye scored ‘failure’, while otherwise ‘success’.

The secondary endpoints of the trial are the time of development of secondary NVG in the study eye up to week 24 (in case aganirsen does not totally inhibit but slows down the development of NVG); the time of development of anterior segment neovascularisation (NVI or NVA); NVD or NVE in the study eye requiring PRP or cryotherapy up to week 24; the development of changes in BCVA (ETDRS letter score) in the study eye up to week 24 (from baseline); the development of needed additional laser treatments and re-treatments in the study eye at up to week 24 including the intensity of the needed additional treatment; the development of changes in the size of retinal nonperfusion areas in the study eye up to week 24 in comparison with the baseline; the development of changes in the National Eye Institute Visual Function questionnaire 25 (NEI-VFQ-25) health questionnaire total score at week 24 in comparison with the baseline; the development of changes in the EuroQoL five dimensions questionnaire (EQ-5D) health questionnaire (validated questionnaires) score at week 24 in comparison with baseline; absolute change from baseline in central retinal thickness in the study eye, assessed by spectral domain optical coherence tomography (SD-OCT) at week 24; NVG classification at 24 weeks on a scale from 1 (non-NVG) to 6 (most advanced NVG) based on central reading of neovascularisation and incidence, causality and intensity of adverse events between the treatment arms.

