All randomised subjects, regardless of treatment group, may receive rescue treatment (e.g. PRP, cryotherapy or other, as routinely performed at the clinical site) at any time during the trial if they progress to anterior segment neovascularisation (NVI or NVA), NVD, or clinically relevant NVE in the fundus. In this case, the primary endpoint is reached and the patient will not further receive study medication. Should a patient receive rescue treatment with intravitreal anti-VEGF (i.e. Lucentis®, Eylea®) because of macular oedema (individual decision of the investigator), the patient will not further receive the study drug, but will be followed up for safety reasons.

The clinical trial will be performed in consideration of the Declaration of Helsinki and the International Conference on Harmonisation – Good Clinical Practice (ICH-GCP). The protocol (Version No.:1.4/Date 7 Jan 2015 Final) is approved by the institutional Ethics Committee from the Landesärztekammer Rheinland-Pfalz, Germany, and by the French Ethics Committee. Ethics approval in other participating countries/sites will follow. Any protocol amendment will be approved by the Ethics Committees and will be distributed to all participating trial sites via the sponsor’s delegated clinical research organisation. Additionally, all necessary documents in the current version will be available on a password-protected website. Personal information of participants will be treated as confidential. Only anonymous data will be forwarded to the sponsor for scientific evaluation. Data entry and storage is performed via an electronic data capture (EDC) system, including plausibility checks.

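### The imaging substudy analyses week-24 images only, so an eye rescued earlier can be labelled NVG on a picture taken after treatment

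*Protocol article*

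**What the plan says.** All references are to the protocol article.

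- **Image time point.** Under Imaging substudy, the analysis has three parts, "all using 24-week data". The three parts are development of the score, its relation to severity, and the comparison of arms. Imaging parameters such as the iris area covered by new vessels are regressed on NVG diagnosis.
- **Case label.** Co-primary efficacy I counts NVG cumulatively to week 24. Any of NVI, NVA, NVD or NVE makes a case, and so does rescue treatment itself.
- **Rescue.** The rescue paragraph after the exclusion criteria says that subjects with neovascularisation "may receive rescue treatment (e.g. PRP, cryotherapy or other, as routinely performed at the clinical site) at any time during the trial". It adds that "the primary endpoint is reached and the patient will not further receive study medication".
- **Follow-up after rescue.** The secondary endpoints count laser treatments and re-treatments up to week 24.
- **Photographs.** Table 1 schedules anterior segment and gonioscopic photography at screening, week 4, week 12 and the visit headed week 24/early termination. Footnote b adds: "Optional at all other visits: only if neovascularisation is suspected".
- **Grade.** A separate secondary endpoint is "NVG classification at 24 weeks on a scale from 1 (non-NVG) to 6 (most advanced NVG) based on central reading of neovascularisation".

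**The concern.** The label covers the whole 24 weeks, while the image shows one day at the end. Between the two, a case may have had PRP or cryotherapy. The Discussion describes PRP as the usual means of reducing retinal ischaemia or neovascularisation, so fewer visible vessels afterwards is the intended result.

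Two things are at stake. First, the score would be trained partly on eyes labelled NVG whose vessels have been treated away, which blurs the relation it is meant to capture. An objective measure of anterior neovascularisation is the declared aim of this substudy. Second, if the arm with more neovascularisation also has more rescued eyes, a week-24 comparison of imaging parameters can understate the difference between arms.

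**Working it through.** The article gives no figure on this point to reproduce. The check sets the rules side by side and then asks how far the planning assumptions can size the problem.

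**1. Following the rules for one eye.** Neovascularisation is found at week 8. The eye is a case under Co-primary efficacy I, and rescue is permitted. Study drug stops, but the subject is not said to leave. The image for analysis is taken at week 24, which is 24 − 8 = 16 weeks later. The label is NVG and the image is post-treatment.

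**2. Does the early-termination heading prevent this?** Not on the text. If rescued subjects stay, as the count of re-treatments to week 24 suggests, their visit 8 falls at week 24, after rescue. If they leave, nothing says the termination images precede rescue, and such images are not week-24 data when taken literally.

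**3. Upper bound on cases.** Inputs from Statistics: 100 placebo and 200 aganirsen evaluable, NVG rates 0.48 and 0.25.

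100 × 0.48 + 200 × 0.25 = 48 + 50 = 98, and 98/300 = 32.7%.

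Two thirds of the data form the learning set: 98 × 2/3 ≈ 65 cases.

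**4. How many could arise early enough to be rescued first?** The Discussion puts average onset near 90 days; week 24 is 24 × 7 = 168 days. The onset distribution is not given, so both patterns below are assumptions.

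- Uniform over 168 days: 98 × 140/168 ≈ 82 before week 20, and 98 × 84/168 = 49 before week 12.
- Exponential with mean m, truncated at day 168: share before day t = (1 − e^(−t/m)) / (1 − e^(−168/m)). For m = 60, 90 and 120 days the shares before week 20 are 96%, 93% and 91% (94, 91 and 90 cases). Before week 12 they are 80%, 72% and 67% (79, 70 and 65 cases).

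Under these assumptions most composite cases arise with time for rescue before the week-24 image. That does not show that they were rescued.

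**5. What is still needed.** Let a be the share of cases with anterior vessels, s the share of those rescued before week 24, and g the share of those whose vessels have regressed by then. The number of label-image mismatches caused by rescue is 98 × a × s × g. The article gives none of a, s or g, so the number lies anywhere from 0 to 98, and reaches 98 only if all three equal 1.

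**6. Direction for the arm comparison.** If a, s and g are equal across arms, the difference in visible anterior neovascularisation at week 24 is (0.48 − 0.25) × a × (1 − s × g). Any s × g above 0 makes it smaller than the pre-rescue difference, 0.23 × a. The direction is towards no difference; the size is open.

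**The case against.** **The label may not be cumulative.** The imaging section does not define NVG diagnosis, so it could mean status at week 24. Label and image would then agree. This is possible, but the only stated NVG rule is the cumulative one, and the arm comparison would still use images taken after rescue.

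**The choice of image belongs in the full protocol or reading manual.** That would be fair if the article were silent. It is not: it fixes the time point for all three parts. The point is about that stated rule.

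**Going back to an earlier image can recreate the fault.** This stands. Without an optional photograph, an eye rescued at week 8 falls back to week 4, and one rescued at week 20 to week 12. Those images may predate the vessels, so the remedy must not pair them with an NVG label.

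**Stronger readings that the article does not support.**

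- A reader might infer that the 23-point planned difference shrinks to 17, 12 or 6 points if 25%, 50% or 75% of cases regress (0.23 × 0.75, 0.50 and 0.25). This sets a = 1. The 23 points belong to a composite that includes NVD, NVE and rescue, whereas the substudy reads anterior segment and gonioscopic photographs. A cap on the score's sensitivity at one minus the regressed share fails for the same reason.
- A reader might infer that cases in general are imaged after treatment. Rescue is permitted, not required, and cases first found at week 24 may be imaged untreated. The Background also describes an irreversible fibrovascular membrane, so signs need not vanish.
- A reader might infer that the six-level grade is also wrongly timed. Grading severity at week 24 regardless of rescue is a legitimate target. Freezing the grade at rescue would hide eyes that worsen despite it.

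**Conclusion.** The concern holds for score development and for the arm comparison of imaging parameters. The stated rules allow a cumulative NVG label to be joined to a post-rescue image, and the early-termination heading does not prevent it. The effect is a weaker score and a possible pull towards no difference between arms.

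The size is not derivable. About 98 of 300 eyes is an upper bound from the planning rates for the composite, and the early-onset shares rest on assumed distributions. The direction for the arm comparison assumes more cases on placebo, as planned, and similar rescue and regression in both arms.

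The imaging analysis is exploratory, and the co-primary tests, sample size and alpha are untouched. This is a minor improvement.

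**What to change.** 1. For score development and the arm comparison of imaging parameters, use for each rescued eye the image set taken at the visit where neovascularisation was detected, before rescue. Footnote b already permits these photographs. Use the week-24 set for eyes never rescued.
2. For a rescued eye without such an image, do not attach an NVG label to an earlier scheduled image. Either leave the eye out of score training, or label each image by the neovascularisation status recorded at that same visit.
3. Report the plain week-24 analysis as a sensitivity analysis.
4. Keep the six-level grade at week 24 as stated. Add the pre-rescue grade only as a supportive analysis.

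The cost is a wording change and an image-selection rule, with no change to clinical management. Image time will differ between eyes, and because event-visit photographs are optional, some rescued eyes will drop out of score training. Eyes with only NVD or NVE may show no anterior vessels whether rescued or not, and this change does not address them.

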#### Biomarker substudy

Statistical analysis of the tear and blood data will be performed in three parts: (1) Identifying factors that discriminate between subjects with and without NVG, (2) Analysing the longitudinal effect of treatment on immunological responses of the eye and (3) Identifying factors that predict a successful outcome of the treatment.

Because this study is exploratory, different statistical classification approaches will be used: (a) Logistic regression, including the process of variable selection and (b) Data mining tools (e.g. supervised clustering and classification trees). To optimise the model parameters, cross-validation and bootstrap methods will be applied. The longitudinal effects of aganirsen versus placebo on immunological responses of the eye will be examined. Essentially, the patterns of immunological response over time in the treatment groups will be examined. This longitudinal effect will be examined by using repeated measures analysis of variance and regression models.

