**Fig. 1 Fig1:**
[figure not shown]
STRONG trial design

Each patient who has signed the Informed Consent Form is monitored for a period of 30 weeks (24-week treatment phase and 6-week safety follow-up) during which patients will attend nine visits (examination schedule in Table 1; see also Fig. 2. (Additional file 1). A computer-based centralised randomisation scheme for all study sites will employ a 1:1:1 treatment assignment ratio (main study) using block randomisation with sequential numbering for each specific trial site. Subjects, investigators, site personnel, monitoring staff, data management and other sponsor personnel, excluding the Clinical Supplies Unit, will be masked to subjects’ assignments. Only in the case of a serious adverse event (SAE), when the masked information is urgently needed for the treatment of the subject, will treatment allocation be revealed.

**Table 1 Tab1:** Examination schedule

Protocol activity	Screening	Baseline	Week 4	Week 8	Week 12	Week 16 + 20	Week 24/early termination	Week 30 (follow-up)
	V1	V2	V3	V4	V5	V6 + 7	V8	V9
Informed consent	X							
Demographic data (age, gender)	X							
Medical and ophthalmic history	X							
Concomitant medications and procedures	X	X	X	X	X	X	X	X
Adverse events	X	X	X	X	X	X	X	X
NEI-VFQ-25/EQ-5D/ Compliance questionnaires		X			X		X	
Vital signs (blood pressure/pulse)	X				X		X	
Electrocardiogram	X						X	
Haematology	X				X		X	
Blood chemistry	X				X		X	
Urinalysis	X				X		X	
Obtain blood sample for risk factor substudy	X							
Obtain blood sample for biomarker substudy	X				X		X	
Pregnancy test (urine or serum)^a^	X							
Physical exam	X							
Best-corrected visual acuity (BCVA) (ETDRS)	X	X	X	X	X	X	X	X
RAPD	X							
Slit lamp biomicroscopy	X	X	X	X	X	X	X	X
Goldmann perimetry/semi-automatic kinetic perimetry	X^d^							
Schirmer test II (biomarker substudy)	X				X		X	
Goldmann applanation tonometry (±1 h)	X^c^	X	X	X	X	X	X	X^c^
Gonioscopy (study eye only)	X	X	X	X	X	X	X	X
Anterior segment and gonioscopic photography^b^	X		X		X		X	
Posterior segment OCT (SD-OCT)	X		X	X	X	X	X	
Indirect ophthalmoscopy	X	X	X	X	X	X	X	X
Fundus photography^b^	X				X		X	
Fluorescein angiography^b^	X				X		X	
Review inclusion/exclusion criteria	X	X						
Randomisation		X						
Administer study treatment (aganirsen or placebo)		X						
Drug dispensing/return and bottle weight		X	X	X	X	X	X	
Patient diary dispensing/return		X	X	X	X	X	X	
Assess rescue treatment criteria			X	X	X	X	X	X

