**Fig. 2 Fig2:**
[figure not shown]
Standard Protocol Items: Recommendations for Interventional Trials (SPIRIT) figure

The two study groups will be treated with aganirsen ‘low-dose’ (43 μg per day) or ‘high-dose’ (86 μg per day). The control group will receive placebo, as there is no labelled treatment for iCRVO to prevent NVG. The placebo is optically identical to the aganirsen emulsion.

Images of the anterior segment and gonioscopic photos of all patients participating in the STRONG study will be collected and evaluated for neovascularisation within the imaging substudy. Tears and serum samples will be collected during the biomarker substudy from 200 patients to evaluate possible markers for both iCRVO and NVG. The results will be compared with results of healthy subjects already available in a German database. Thirty-three eligible patients will be included in the risk factor substudy across all participating trial sites. At UMC Mainz, 33 age- and gender-matched healthy controls will be recruited. Blood samples will be collected to analyse laboratory parameters for coagulation and fibrinolysis and genetic factors to identify risk factors for iCRVO.

Protocol assistance at the European Medicines Agency (EMA) has taken place to define patients with a high risk for developing NVG. The inclusion criteria must be fulfilled at both the screening and baseline visits.

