### Statistics

Presentation of the sample size is based on both aganirsen doses combined demonstrating superiority placebo on the co-primary endpoints of neovascularisation and IOP at 24 weeks. Calculation of the sample size is based on the following: (1) An aganirsen to placebo ratio of 2:1, (2) Neovascularisation measured dichotomously (NVG = yes/NVG = no) with estimated disease rates in the population of 0.25 for aganirsen and 0.48 for placebo. Testing of neovascularisation will be done using the normal approximation to the chi-square distribution for consistency with O’Brien-Fleming Alpha spending, which is also computed based on normal approximation, (3) IOP measured dichotomously with estimated rates of events in the population of 0.24 for aganirsen and 0.41 for placebo at 24 weeks and (4) Up to four performed analyses. Based on albeit heterogeneous historical data, we estimate that 25% of subjects in the aganirsen group and 48% in the placebo group will develop NVG by 24 weeks. Given a 2:1 aganirsen to placebo assignment ratio, a total of 300 evaluable subjects – 200 with aganirsen and 100 with placebo – will provide 80% power to reject the null hypothesis that aganirsen is no better than placebo. Power computation is based on the chi-square test with a two-sided alpha = 0.05. Assuming that approximately 10% of subjects will not be evaluable due to loss to follow-up and other reasons, a total of 333 subjects are planned for this trial. Missing values of NVG and IOP will be imputed using the last observation carried forward (LOCF) method.

Primary efficacy will be assessed up to four times: two initial futility analyses, followed by an interim analysis for success/futility/continuation and a final analysis. The data will be summarised in tables listing the mean, standard deviation, minimum, median, maximum and number of subjects in a group for continuous data or in tables listing count and percentage for categorical data, where appropriate. Data listing by subject will be provided. The effects of noncompliance, dropouts and covariates, and their interactions with treatment will be assessed to determine the impact on the general applicability of results from this study. Secondary comparisons will be considered exploratory, so that there will be no Type I error adjustment for multiple secondary comparisons.

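### Exploratory biomarker comparison: a baseline-adjusted mixed model with a joint test at weeks 12 and 24 would use the samples better than the repeated-measures ANOVA named in the article

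*Protocol article*

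**What the plan says.** The Biomarker substudy section of the protocol article lists three analyses. The second is the effect of treatment on immunological responses over time, aganirsen against placebo. Its aim is put this way: "Essentially, the patterns of immunological response over time in the treatment groups will be examined". The method follows: "This longitudinal effect will be examined by using repeated measures analysis of variance and regression models". The section calls itself exploratory ("Because this study is exploratory, different statistical classification approaches will be used") and gives no effect size, alpha or power.

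The substudy size is in Methods/design: "Tears and serum samples will be collected during the biomarker substudy from 200 patients". In Table 1 the row "Obtain blood sample for biomarker substudy" is marked at screening, week 12 and week 24, and the Schirmer test row for tears is marked at the same three visits. Study drug is first given at the baseline visit, so each patient has one sample before treatment and two on treatment.

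Two other statements bear on the point. The Secondary efficacy analysis section uses ANCOVA with the baseline value as covariate for continuous changes to week 24. The Statistics section gives a missing-data rule (LOCF) for NVG and IOP only, and plans the main trial for some loss: "Assuming that approximately 10% of subjects will not be evaluable due to loss to follow-up and other reasons".

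**The concern.** Treatment cannot affect the screening sample. If that sample is one of three outcome levels, as in classical repeated-measures ANOVA, two things follow. The arm main effect averages a guaranteed zero with the two real effects. The arm-by-time test, which is the relevant one for a pattern over time, works on differences from screening and does not adjust for the screening level. Differencing subtracts the whole screening value, whereas adjustment subtracts only the part that predicts the later values, so differencing leaves more noise unless the within-patient correlation is high.

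The classical form also needs complete rows. A patient with a screening and a week-12 sample but no week-24 sample would contribute nothing.

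At stake is the substudy's only stated comparison of aganirsen with placebo over time. Samples from 200 patients with a rare disease are hard to collect again, and a null result from a weaker test could be read as absence of a biological effect.

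**Working it through.** **The plan's own figure.** The article gives no power for this comparison. Its only power figure is 80% for the co-primary endpoints with 200 v 100 patients. At the final alpha of 0.04288 that recomputes to 97.4% (neovascularisation, 0.25 v 0.48) and 83.7% (IOP, 0.24 v 0.41). The product is 0.974 × 0.837 = 0.815 if the two are independent, in line with 80%. The biomarker analysis does not enter it.

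**Inputs from the article.** 200 patients; 1:1:1 randomisation, hence 2:1 for both doses combined against placebo; samples at screening, week 12 and week 24.

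**Assumptions.** The substudy follows the main ratio and pools the doses (200 × 2/3 ≈ 133 v 67). SD is 1 at each visit, with equal correlation ρ between visits of 0.3, 0.5 or 0.7. The effect is 0.4 SD. Each marker is tested at two-sided 5%, with no missing samples. Three effect shapes at weeks 12 and 24: constant (0.4, 0.4), one visit only (0, 0.4), growing (0.2, 0.4).

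**Formulas.** f = 1/133 + 1/67 = 0.02244.

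- Arm-by-time ANOVA (2 and 396 df): λ = SS/[(1−ρ)f], where SS is the sum of squared deviations of the three arm differences (0, d₁₂, d₂₄) from their mean.
- Baseline-adjusted joint test (2 and 196 df): λ = [a(d₁₂² + d₂₄²) − 2b·d₁₂·d₂₄]/[(a² − b²)f], where a = 1−ρ² and b = ρ−ρ² are the variance and covariance of the two later values given screening.
- Power comes from the noncentral F distribution with that λ.

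**Worked at ρ = 0.5** (a = 0.75, b = 0.25, a² − b² = 0.50).

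- ANOVA, constant effect: SS = 0.1067, λ = 0.1067/(0.5 × 0.02244) = 9.51, power 79%. For one visit only SS is also 0.1067, so power is the same.
- Joint test, constant effect: (0.75 × 0.32 − 0.50 × 0.16)/0.50 = 0.32; λ = 0.32/0.02244 = 14.26, power 93%.
- Joint test, one visit only: 0.75 × 0.16/0.50 = 0.24; λ = 10.69, power 84%.
- Joint test, growing effect: (0.75 × 0.20 − 0.50 × 0.08)/0.50 = 0.22; λ = 9.80, power 80%. For ANOVA, SS = 0.08, λ = 7.13, power 66%.

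**Power (%), arm-by-time ANOVA v joint baseline-adjusted test, no missing samples**

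| Effect shape | ρ = 0.3 | ρ = 0.5 | ρ = 0.7 |
|---|---|---|---|
| Constant | 63.8 v 89.7 | 79.1 v 92.9 | 95.3 v 98.3 |
| One visit only | 63.8 v 72.6 | 79.1 v 83.6 | 95.3 v 96.3 |
| Growing | 50.8 v 73.5 | 66.0 v 80.1 | 87.7 v 92.6 |

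**The ANOVA main effect** is weaker still. For a constant effect at ρ = 0.5, the mean difference is 0.8/3 = 0.267 and its standard error is √[(1+2ρ)/3 × f] = √(0.667 × 0.02244) = 0.122. Then z = 2.18 and power is 59%.

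**Missing samples.** If 5% miss week 12 and 10% miss week 24 independently, 0.95 × 0.90 = 85.5% of rows are complete. The complete-case arm-by-time power for a constant effect falls from 64/79/95% to about 57/72/92%. These missing rates are assumed; the article gives none for biomarker samples.

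**Testing the average first.** A 1-df baseline-adjusted test of the mean of both visits has variance [(1+ρ)/2 − ρ²]f. At ρ = 0.5 with an effect at one visit only, z = 0.2/√(0.5 × 0.02244) = 1.89 and power is 47%, below the ANOVA's 79%. The choice of joint test over average therefore matters.

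**The case against.** The sentence names regression models as well as ANOVA, and these could include the very model proposed here. No section says that the screening sample is an outcome level or that patients with a missed sample are dropped. Covariate roles and missing-sample handling are commonly left to a full protocol or SAP, and neither is shown. All of this stands. A reader might infer that ANOVA is the only method, or that the plan excludes patients with usable data; the article supports neither. What remains is that the one specific method named is, in its standard form, the weaker choice for this schedule.

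A reader might also infer that the trial loses power it was designed to have. It does not: the substudy is labelled exploratory and has no power target.

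A further objection is that the size of the loss depends on the effect shape, and that the stated interest is in patterns over time. This is right about any proposal that leads with the average effect, which can do worse than the ANOVA when the effect differs by visit. It does not reach the joint 2-df test, which was ahead for every shape and correlation tried. Nor do the two tests ask different questions: randomisation makes the expected screening means equal, so parallel profiles over three visits and no arm difference at either later visit are the same null hypothesis.

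Finally, the ANCOVA in the Secondary efficacy analysis concerns change to a single time point, so the different method here is not a contradiction. It shows only that baseline adjustment is already accepted elsewhere in the plan.

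**Conclusion.** The point holds as a low-severity improvement. Nothing in the article is misstated. If the named ANOVA is run in its classical form, the arm-by-time test has about 64% to 95% power for a 0.4 SD effect, constant or at one visit only. The joint baseline-adjusted test has 90% to 98% (constant) or 73% to 96% (one visit only).

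The gain is largest at low correlation: about 26 points for a constant effect at ρ = 0.3. It is small at high correlation: 1 to 3 points at ρ = 0.7 for these two shapes. All of these figures rest on assumed effect size, correlations, equal variances and a 133 v 67 split with doses pooled. Only the number of patients, the allocation ratio and the sampling times come from the article. The co-primary analyses are untouched.

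**What to change.** In the Biomarker substudy section, or in the SAP, replace repeated-measures ANOVA for the aganirsen v placebo comparison with a mixed model for repeated measures:

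- Outcomes: the week-12 and week-24 values of the marker, on the log scale where skewed.
- Fixed effects: arm, visit, arm-by-visit, and the screening value of the same marker as covariate.
- Unstructured covariance between the two visits; all patients with at least one post-baseline sample. This takes missed samples as missing at random given the observed data, which should be stated.
- Test arm jointly at the two visits (2 df) first. Then report the arm difference at each visit and the average, with confidence intervals.

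The cost is a sentence or two of text. No sample, visit or patient is added, and the Trial status section says recruitment had not opened, so the change can precede any data.
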